They will provide the following:Nursing assessment: to allow comparison between the two groups, the questionnaires described in Table 1 will be used at baseline and according to the timing described in Table 1. The measurements will allow researchers to highlight the effectiveness of the telenursing intervention and the improvement of patients’ clinical path.Support in study procedures: during the 6-month follow-up, nurses will provide advice to the patients involved to improve the experience with the intervention and the tools used, and also in order to optimize the data collection in the two compared groups.Intervention in the IA: with patients involved in the experimental group, research nurses will use telenursing to monitor the supportive care needs and other objectives described in Section 1.2. For the purposes of the study, the telenursing intervention will use the Intelligence2health platform for video calls, a dedicated telephone line, short messages and electronic tools. During the 6-month study, nurses will implement a total of 8 video calls. Nurses will implement patient education interventions to improve patient care, quality of life, satisfaction, treatment adherence, problem-solving skills, and self-care. Suggestions to better manage patients’ needs will be evidence-based and may be agreed with medical oncologists as needed. However, they will be kept constantly updated on the health status of patients. Nursing interventions will be aimed at promoting the care needs of patients.Data collection will be carried out using the chosen tools, according to the timing described in Table 1, at baseline, daily, after 30, 90 and 180 days, to allow comparison between the intervention arm and control arm. In particular, patients and nurses will monitor the burden and needs related to care through the Supportive Care Needs scale [18,19]; therapeutic adherence through the MARS-5I [24,25]; QoL through the QoL SF-36 [20,21]; satisfaction and usability of the system through the SUS [22,23]; performance status through the Karnofsky performance status [26]; and the AEs described in Section 1.2 through the CTCAE tools [27]. Patients enrolled in the control group will use paper questionnaires, while patients in the intervention group will use electronic tools that nurses will check daily to implement any coaching interventions. Any changes in the health status or needs of patients can be intercepted early thanks to the filling out of daily forms by the patients themselves, which nurses will check daily.Creation and management of a specific database.

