
After nurses have obtained the informed consent, 40 patients with melanoma and lung cancer (20 in each group) will be randomised into the IA (telenursing intervention added to clinical practice) or the CA (clinical practice). To allow for comparison, at baseline (T0) before the randomisation, patients from both groups will complete the tools shown in Table 1 in paper format. Additionally, patients involved in the study will use the study tools according to the timelines described in Table 1 at T1 (30 days), T2 (90 days), and T3 (180 days). Regarding the practice procedures, monthly telenursing interventions will be provided every 30 days, on dates agreed in advance with patients. However, patients will be able to communicate with the nursing staff via short messages or by telephone at any time of the day, between 8 a.m. and 2 p.m. An unplanned nursing intervention can be useful in case of patient doubts or problems related to therapeutic adherence (dosage errors, forgotten or double doses, etc.), onset of new side effects, sudden alterations in vital signs, etc. In addition, in view of the daily questionnaire filled out by patients (Table 1), nursing staff will implement additional interventions as needed, remotely or in person.

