#### 2.4.1. Control Arm

The CA patients will attend monthly visits with oncologists and receive in-person nursing care as needed. They will fill out paper-form questionnaires collected by nurses during the monthly visits until the end of the study. Nurses and oncologists will not consider patient data during follow-up, and according to clinical practice, patients should contact oncologists as needed. Data collected by nurses during the monthly visits and by patients at home will be recorded in a specific database by the nurses, but these data will not be evaluated by nurses or oncologists during the study. However, according to current clinical practice, if necessary, patients in the control group will be able to contact oncologists and nurses via the telephone and email addresses provided before the start of the study.

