#### 2.4.2. Intervention Arm

In addition to clinical practice, after the randomisation, the IA patients will receive an educational nurse intervention to improve the SCNs [18,19], prevent the main AEs and recap the study procedures. Furthermore, at baseline, the IA patients will receive the following:A link to access the electronic questionnaires through a web platform (GDPR and privacy compliant) (daily, at one, three and six months).A link to access the platform Intelligence2health [30], actually used in the same national cancer centre for the monthly telenursing interventions.A company telephone number to contact the team nurses.

In the first month, nurses involved in the study will carry out two telenursing interventions through a video call enabled by the platform (Table 2). The first virtual meeting will be conducted seven days after baseline (T0), focusing on the study procedures and e-tools. Subsequent telenursing interventions will be carried out monthly. Research nurses will review the daily data from the IA patients to arrange appropriate reinforcement interventions (coaching), agreed upon with oncologists where applicable. However, the oncologists will be steadily updated on the patients’ clinical conditions. The telenursing interventions will aim to prevent, monitor and improve treatment-related outcomes (Table 1). Specifically, evidence-based nursing coaching interventions will aim to improve the SCNs [18,19], adverse events and vital signs described in the primary and secondary objectives, and what will be required by patients regarding treatment-related needs.

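### At T1 the primary questionnaire is collected electronically, through a channel nurses check, in the intervention arm but on unevaluated paper in the control arm, so a reporting shift cannot be told from a treatment effect

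*Protocol article*

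**What the plan says.** The primary objective (section 1.2) is supportive care needs at T1, one month into treatment. Table 1 names the patient as respondent for this scale at T0, T1, T2 and T3. Section 2.5 states that neither patients nor healthcare professionals are blinded.

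How the forms are collected:

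- **T0, before randomisation (section 2.4):** "patients from both groups will complete the tools shown in Table 1 in paper format". The stated purpose is comparability.
- **Intervention arm after T0 (section 2.4.2):** patients receive "A link to access the electronic questionnaires through a web platform (GDPR and privacy compliant) (daily, at one, three and six months". Section 2.6 confirms that this arm's data come in electronically.
- **Control arm after T0 (section 2.4.1):** "They will fill out paper-form questionnaires collected by nurses during the monthly visits until the end of the study".
- **Both arms side by side (section 2.4):** "Patients enrolled in the control group will use paper questionnaires, while patients in the intervention group will use electronic tools that nurses will check daily". The purpose of the check is coaching, since these are "electronic tools that nurses will check daily to implement any coaching interventions". The SCN scale is among the tools listed just before.
- **Handling of control data (section 2.4.1):** nurses enter the forms in a database, but "these data will not be evaluated by nurses or oncologists during the study".

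Section 2.4.2 has the research nurses both review the intervention arm's daily data and deliver the coaching. The limitations in section 3.1 do not mention the difference in collection.

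**The concern.** A self-reported score reflects the patient's state and also how, and for whom, the form is filled in. Here both of the latter can differ by arm at the primary time point. One arm answers on a web form belonging to a set of tools that the coaching nurses check. The other answers on paper that nobody assesses during the trial.

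A needs scale is open to this in either direction. A patient may report fewer needs to a nurse who has been helping, or more needs if reporting them brings help. The first would exaggerate a benefit and the second would hide one.

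The t test or Mann–Whitney test planned in section 2.7 compares the arms as observed and cannot separate a change in reporting from a change in need. Adjusting for T0 would not help either, because T0 is on paper for everyone and only the intervention arm changes mode between T0 and T1.

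**Working it through.** **1. Collection conditions by arm and time**

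| | T0 | T1 (primary) |
|---|---|---|
| Intervention, mode | paper | electronic (2.4.2, 2.6) |
| Control, mode | paper | paper (2.4, 2.4.1) |
| Intervention, handling | before randomisation | electronic tools checked daily by nurses, to trigger coaching (2.4) |
| Control, handling | before randomisation | collected and entered by nurses, not evaluated (2.4.1) |

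Conditions match at T0 and differ at T1. Write the observed T1 difference as treatment effect plus *b*, where *b* is the reporting shift caused by the arm-specific channel. At T0 *b* = 0 in both arms, so the baseline score carries no information about *b*. It therefore stays in the estimate with or without baseline adjustment.

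**2. The plan's own figures (section 2.2)**

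Inputs: means 81.53 and 103.5, SDs 13.2 and 21.96, two-sided α = 0.05, power 90%, drop-out 20%.

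- Difference: 103.5 − 81.53 = 21.97 points.
- Pooled SD: √((13.2² + 21.96²)/2) = √((174.24 + 482.24)/2) = √328.24 = 18.12.
- Effect size: 21.97/18.12 = 1.21, as stated.
- Exact t-test power: 89.3% at 15 per arm and 91.3% at 16, so 16 per arm (32 in total), as stated.
- Drop-out: 32/(1 − 0.20) = 40, as stated.

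The sample size is sound on its own inputs, and the present point does not depend on it.

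**3. Illustration of size**

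The documents give no mode or handling effect. Assume a shift of 0.1 to 0.3 SD:

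- 0.1 × 18.12 = 1.8 points; 1.8/21.97 = 8% of the planned difference.
- 0.3 × 18.12 = 5.4 points; 5.4/21.97 = 25% of the planned difference.

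Under the same assumption, with no true treatment effect and SD 18.12, the two-sided t test rejects at these rates (noncentral t):

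| Assumed shift | 16 per arm | 20 per arm |
|---|---|---|
| 0 | 5.0% | 5.0% |
| 0.1 SD | 5.9% | 6.1% |
| 0.2 SD | 8.5% | 9.5% |
| 0.3 SD | 13.0% | 15.2% |

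These figures show what such a shift would do if present. They are not evidence that it is.

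**The case against.** The strongest reply is that much of the asymmetry is the treatment. Section 2.4 includes electronic tools in the telenursing intervention and has nurses use it to monitor supportive care needs, so reporting to a responsive nurse is part of what is being tested. That stands for the daily forms, and nothing here asks for them to change. It does not extend to the scheduled SCN form, which is the yardstick for both arms and need not travel through one arm's channel.

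It is also fair to say that blinding is impossible. Unblinded self-report will remain whatever is done. Different modes and handling are a further difference, and that one can be avoided.

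Four stronger readings are tempting, but the documents do not support them:

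- **A telenursing call falls on the day of the T1 form.** A reader might infer this because "monthly telenursing interventions will be provided every 30 days" and T1 is day 30. But the same sentence leaves the dates to prior agreement with patients, and section 2.4.2 places the first call seven days after baseline, with two calls in the first month. No section puts a call on the day of the T1 form. The order of call and form is detail that an article may leave to the full protocol.
- **The control forms are unread.** Nurses collect and transcribe them. The text says only that the data are not evaluated or considered during the study.
- **Nurses are expressly said to read the T1 SCN form, and patients know it.** Section 2.4 applies daily checking to the electronic tools in general, after listing the SCN scale. The more specific statements concern the daily forms and daily data. Review of the T1 form is a reasonable inference. Patients' awareness of it is not stated at all.
- **The bias is known to favour telenursing or to be large.** Neither direction nor size can be obtained from the documents. On the assumed range, 75% to 92% of the planned difference would still be treatment effect.

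**Conclusion.** The point holds in a limited form. It is explicit that the primary form at T1 is electronic in one arm and paper in the other, after a common paper form at T0. It is also explicit that the electronic tools are checked to trigger coaching while the control data are not evaluated. Collection mode and handling therefore differ by arm at the primary time point, and neither the planned tests nor baseline adjustment can remove a resulting shift.

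The size is unknown. The range of 1.8 to 5.4 points (8% to 25% of 21.97) rests wholly on an assumed 0.1 to 0.3 SD and on the pooled SD of 18.12 from section 2.2. If the true effect is smaller than the large one planned, the same shift would make up a larger share of the estimate. The change should be made because it concerns the primary endpoint and is cheap. It does not show that the trial's result would be wrong.

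**What to change.** Collect the scheduled T1, T2 and T3 patient questionnaires (SCN, SF-36, MARS-5I) in one mode in both arms. Either option works:

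- self-completed paper at the monthly follow-up visit that Table 2 gives both arms, which also matches T0; or
- the same web form for everyone, which is feasible because section 2.3 requires every patient to have internet access and a device. The mode would then change after T0 alike in both arms.

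In both arms, have the form completed before that visit's nurse contact, and state that the scheduled outcome answers are not used to trigger coaching. A rule on use is more workable than hiding the forms from the nurses, because the nurses themselves enter them in the database. Leave the daily e-forms and their review as the intervention's monitoring tool.

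The cost is a protocol amendment plus paper forms or web access for 20 patients. The sample size stays at 40. The downside is that intervention nurses would not act on the scheduled SCN answers, though they keep the daily data. If the change is not made, the asymmetry should be listed among the limitations in section 3.1.

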#### 2.4.1. Control Arm

The CA patients will attend monthly visits with oncologists and receive in-person nursing care as needed. They will fill out paper-form questionnaires collected by nurses during the monthly visits until the end of the study. Nurses and oncologists will not consider patient data during follow-up, and according to clinical practice, patients should contact oncologists as needed. Data collected by nurses during the monthly visits and by patients at home will be recorded in a specific database by the nurses, but these data will not be evaluated by nurses or oncologists during the study. However, according to current clinical practice, if necessary, patients in the control group will be able to contact oncologists and nurses via the telephone and email addresses provided before the start of the study.

#### 2.4.2. Intervention Arm

In addition to clinical practice, after the randomisation, the IA patients will receive an educational nurse intervention to improve the SCNs [18,19], prevent the main AEs and recap the study procedures. Furthermore, at baseline, the IA patients will receive the following:A link to access the electronic questionnaires through a web platform (GDPR and privacy compliant) (daily, at one, three and six months).A link to access the platform Intelligence2health [30], actually used in the same national cancer centre for the monthly telenursing interventions.A company telephone number to contact the team nurses.

In the first month, nurses involved in the study will carry out two telenursing interventions through a video call enabled by the platform (Table 2). The first virtual meeting will be conducted seven days after baseline (T0), focusing on the study procedures and e-tools. Subsequent telenursing interventions will be carried out monthly. Research nurses will review the daily data from the IA patients to arrange appropriate reinforcement interventions (coaching), agreed upon with oncologists where applicable. However, the oncologists will be steadily updated on the patients’ clinical conditions. The telenursing interventions will aim to prevent, monitor and improve treatment-related outcomes (Table 1). Specifically, evidence-based nursing coaching interventions will aim to improve the SCNs [18,19], adverse events and vital signs described in the primary and secondary objectives, and what will be required by patients regarding treatment-related needs.

### 2.5. Fidelity of Intervention and Randomisation

Nurses will prevent and manage both groups of patients’ toxicities and needs according to good clinical practice [31], in collaboration with the oncologists.

The random sequence of eligible patients in the CA and the IA will be 1:1. The assignment list will be generated by special software before the study starts, and it will be unknown to the nurses and the oncologists. Due to the nature of the interventions, the patients and healthcare professionals will not be blinded. In case of system dysfunctions or desire to leave the study, all the patients will be followed according to the current clinical practice by healthcare teams.

Patients may drop out of the study at any time without affecting their care pathways, which will continue to be provided according to current clinical practice. At the same time, patients who do not adhere to the study procedures may be excluded from the study after 15 days of missing data.

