### 2.6. Data Collection

The planning of the study will include an enrolment period lasting 12 months, starting from the involvement of the first patient after 15 June 2024. The study follow-up will last six months. After this period, all the patients will be referred to current clinical practice. Nurses will record digital data from patients’ self-reports and nurses’ interviews and observations in a specific database.

Patients in the control arm will be treated according to current clinical practice, mainly with the support of oncologists. The paper questionnaires that patients and nurses will complete during the study will be recorded by nurses in a specific database.

Data from patients enrolled in the intervention group will be collected via electronic questionnaires, similar to those of nurses. Data collection for the outcomes described in Table 1 will be assessed at baseline (T0), after 30 (T1), 90 (T2) and 180 days (T3). In addition, patients will transmit data daily relating to the monitoring of vital parameters and AEs described in the section on the primary and secondary objectives.

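### Section 2.5 falls back to current clinical practice, the control condition, for a system fault as well as for a wish to leave; telenursing could continue by telephone or message instead

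*Protocol article*

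**What the plan says.** The rule is in section 2.5 of the protocol article, on fidelity of the intervention and randomisation: "In case of system dysfunctions or desire to leave the study, all the patients will be followed according to the current clinical practice". It gives no time limit, no return to telenursing after a fault, and no alternative channel.

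Section 2.4 defines the two arms as "IA (telenursing intervention added to clinical practice) or the CA (clinical practice"). Section 2.6 repeats the control condition: "Patients in the control arm will be treated according to current clinical practice, mainly with the support of oncologists".

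Only the intervention arm relies on the trial's technical systems. In the first month, before the primary endpoint, "nurses involved in the study will carry out two telenursing interventions through a video call enabled by the platform" (section 2.4.2). Coaching depends on the daily forms: "patients in the intervention group will use electronic tools that nurses will check daily to implement any coaching interventions" (section 2.4). Control patients use paper.

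The intervention has other channels too. Section 2.4 states that "the telenursing intervention will use the Intelligence2health platform for video calls, a dedicated telephone line, short messages and electronic tools", and that "patients will be able to communicate with the nursing staff via short messages or by telephone" during set daytime hours. Section 2.4.2 gives each intervention patient a number for the team nurses. Paper versions of the questionnaires also exist, since at baseline "patients from both groups will complete the tools shown in Table 1 in paper format".

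**The concern.** A patient who wants to leave and a platform that stops working are different events. The first is the patient's decision, and a return to usual care is the proper response. The second is a fault in the trial's own delivery system, in a patient who still wants the intervention. Giving both the same fallback means that, if staff follow the sentence, a fault replaces the experimental care with the comparator for as long as it lasts.

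The effect falls on one arm. Controls have no video platform or electronic forms to lose, so nothing changes for them. Intervention patients lose the scheduled, nurse-initiated contact, or the coaching prompted by daily review, or both. Patient-initiated telephone contact does not by itself preserve the contrast, because section 2.4.1 lets control patients telephone nurses as well.

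Section 2.7 plans an intention-to-treat analysis. Affected patients would be analysed in the intervention arm after receiving less of the intervention, which pulls the one-month difference in supportive care needs towards zero.

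**Working it through.** **Reproducing the planned sample size (section 2.2).** Inputs: mean 81.53 (SD 13.2) with intervention, 103.5 (SD 21.96) with control, two-sided Student t test, α = 0.05, power 90%.

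- Difference: 103.5 − 81.53 = 21.97.
- Common SD: √((13.2² + 21.96²)/2) = 18.12. Effect size: 21.97/18.12 = 1.21, as stated.
- With 16 per arm: standard error = √(13.2²/16 + 21.96²/16) = 6.41; noncentrality = 21.97/6.41 = 3.43; power from the noncentral t with 30 degrees of freedom = 0.913. With 15 per arm it is 0.893, so 16 is the smallest adequate number.
- 32/(1 − 0.20) = 40, as stated. If all 20 per arm are evaluable, power is 0.962.

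The sample size is correct and is not in dispute.

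**Scenarios for one fault.** The protocol gives neither a fault rate nor a duration. Assumptions: 20 intervention patients enrol evenly over the 12-month enrolment period of section 2.6 (taken as 365 days); there is one fault of d days; each patient has 30 days and two scheduled calls before T1; all benefit is lost on each fault day; a missed call is not rescheduled; the one-month benefit falls in proportion to the days lost; the SDs are unchanged.

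- Scheduled first-month calls hit: 20 × 2 × d/365.
- Patient-days before T1 lost: 20 × 30 × d/365 = 600d/365, a share of d/365.
- Diluted difference: 21.97 × (1 − d/365).

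| Fault (days) | Calls hit | Patient-days lost (share) | Difference | Power, 16 per arm | Power, 20 per arm |
|---|---|---|---|---|---|
| 0 | 0 | 0 | 21.97 | 0.913 | 0.962 |
| 1 | 0.11 | 1.6 (0.3%) | 21.91 | 0.911 | 0.961 |
| 7 | 0.77 | 11.5 (1.9%) | 21.55 | 0.902 | 0.956 |
| 14 | 1.53 | 23.0 (3.8%) | 21.13 | 0.891 | 0.949 |
| 30 | 3.29 | 49.3 (8.2%) | 20.16 | 0.861 | 0.929 |

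These losses are on the high side. Section 2.4.2 lists two separate links, one to the electronic questionnaires and one to the video platform, and nothing says that they fail together. A video fault need not stop the daily forms, and a forms fault need not stop the calls.

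**The same question by patient (simulation).** If one or two intervention patients each lose a quarter of the effect, power is 0.902 or 0.889 with 16 per arm, and 0.956 or 0.951 with 20 per arm. If one or two lose all of it, power is 0.853 or 0.779 (16 per arm), and 0.933 or 0.892 (20 per arm). Complete loss is an upper bound. A short outage would not cause it, because the educational session after randomisation has already been given and the first call covers study procedures and the electronic tools.

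**The case against.** The strongest reply is that the sentence only promises a floor of care. Intervention patients receive telenursing on top of clinical practice, so saying that they will be followed under clinical practice need not mean that telenursing stops. Telephone and messages are already part of the intervention and are nowhere withdrawn. That may well be the intent. It fits the sentence poorly, though: for patients who leave, the same words plainly mean clinical practice in place of telenursing, and no separate meaning is given for a fault. Nor does any passage move a scheduled call to the telephone.

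A second reply is that telenursing as delivered, outages included, is a legitimate pragmatic estimand, and that operational detail belongs in the full protocol. The first part is fair, and is one reason why this is minor. The second does not dispose of the point, which concerns a rule the article states.

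That telephone contact would serve as well as video is an inference, since section 2.4 describes telephone and messages mainly for patient-initiated or unplanned contact.

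A reader might infer several stronger things that the text does not support:

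- **Affected patients change arm or leave the study.** The sentence does not end allocation or the T1 to T3 assessments.
- **Power falls sharply.** If 10% to 30% of intervention patients reverted fully before T1, power with 16 per arm would be 0.81 to 0.53, but no figure in the protocol suggests that proportion or a complete loss of effect.
- **The result could be biased in favour of telenursing.** The dilution described here runs the other way.
- **Patients caught in a fault would be excluded under the 15-day missing-data rule.** That rule concerns patients who do not adhere and is permissive, so a fault is not clearly within it.

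**Conclusion.** The point holds as a minor one. Section 2.5 gives a technical fault the control condition as its fallback, although the trial already has other means of delivering the intervention. Followed as written, it would interrupt telenursing in one arm only and slightly dilute the primary contrast.

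The direction is conservative. The cost is about one percentage point of power or less for a single outage of up to a week, and about five points with 16 per arm (0.913 to 0.861) or three with 20 per arm (0.962 to 0.929) for a month-long fault that stops all channels. These sizes rest on an assumed single fault, even enrolment and benefit proportional to days of exposure; the 16-per-arm figures also presuppose the planned 20% drop-out. The true frequency and length of faults are unknown.

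**What to change.** Split the sentence in section 2.5. Suggested content for a system dysfunction:

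- The patient stays in the study and in the allocated arm.
- Scheduled telenursing contacts and coaching continue by the dedicated telephone line or short messages, or in person, until the system is restored.
- Any T1, T2 or T3 questionnaire falling due is completed on the existing paper forms.

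Keep the present wording only for patients who ask to leave. Two optional clarifications are to flag paper completion in the database and to state that gaps caused by a fault do not count as non-adherence under the 15-day rule.

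The cost is a short amendment using resources the trial already has. The downside is that a few intervention-arm questionnaires would be on paper and some contacts by telephone instead of video.

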### 2.7. Data Analysis

Intention-to-treat analysis will be applied in case of abandonment of a patient from one arm or the other. The rigor observed in the study will be aimed at acquiring detailed and exhaustive information. However, missing data due to incomplete or partial registration by the patient will be treated with appropriate statistical techniques. Descriptive statistics will explore the continuous variables through the means and standard deviations (±SD), while the categorical variables will explore the absolute frequencies and percentage values. The Kolmogorov–Smirnov normality test will be used for all the continuous variables. The Chi-square or Fisher’s exact test will assess the potential associations between categorical variables. The differences for continuous variables will be explored using the nonparametric Mann–Whitney U test or Student’s *t* test, depending on the nature of the distributions of the variables examined. All the statistical analyses will be performed using Statistical Package for the Social Sciences (SPSS) Software 29.0 (IBM SPSS Statistics for Windows, Version 29.0. Armonk, NY, USA: IBM Corp.) for Windows. A *p*-value < 0.05 will be considered statistically significant.

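### The 15-day missing-data exclusion rule conflicts with intention-to-treat and is liable to remove patients unequally before the day-30 primary outcome

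*Protocol article*

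**What the plan says.** Section 2.5 first lets patients leave the study at will, then adds a separate rule: "patients who do not adhere to the study procedures may be excluded from the study after 15 days of missing data". The rule is permissive, names no arm, and does not say who decides or what becomes of the patient's data. The same section states that patients and healthcare professionals are not blinded.

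On analysis, section 2.7 says: "Intention-to-treat analysis will be applied in case of abandonment of a patient from one arm or the other". It adds that "missing data due to incomplete or partial registration by the patient will be treated with appropriate statistical techniques".

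The data that could be missing for 15 days within the first month are the daily ones. Section 2.6 says: "In addition, patients will transmit data daily relating to the monitoring of vital parameters and AEs". In Table 1 everything else is monthly or at T0, T1 (30 days), T2 (90 days) and T3 (180 days). The primary outcome is the supportive care needs score at T1.

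The arms differ in how these data are captured. Section 2.4: "Patients enrolled in the control group will use paper questionnaires, while patients in the intervention group will use electronic tools that nurses will check daily". Section 2.4.1, on control patients: "They will fill out paper-form questionnaires collected by nurses during the monthly visits until the end of the study". Of the control data it also says that "these data will not be evaluated by nurses or oncologists during the study".

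**The concern.** Intention-to-treat needs outcome data from every randomised patient, or at least a genuine attempt to get them. A rule that takes patients out for not completing forms works against this. The intention-to-treat sentence covers a patient who abandons an arm, and removal by the study team is not abandonment. The missing-data sentence covers incomplete registration by the patient, not a patient who has been taken out. A patient excluded before day 30 would ordinarily have no T1 score, and the trial would have created that gap itself.

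The second problem is that a lapse becomes visible at different times in the two arms. If lapsing is related to supportive care needs, and early exclusions fall mainly in one arm, the patients left at T1 are no longer comparable as randomised. Therapeutic adherence (MARS-5I) is a secondary outcome, so selection on adherence to study procedures may affect it too.

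**Working it through.** **1. The plan's own figures (section 2.2).** Inputs: means 81.53 and 103.5, SDs 13.2 and 21.96, two-sided α = 0.05, power 90%, drop-out 20%.

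- Pooled SD = √((13.2² + 21.96²)/2) = √328.24 = 18.12
- Effect size = (103.5 − 81.53)/18.12 = 21.97/18.12 = 1.21, as stated
- Power from the noncentral t: 89.3% at 15 per arm and 91.3% at 16 per arm, so 16 per arm (32 in total) is right
- 32/(1 − 0.20) = 40, as stated

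The sample size reproduces and is not in question.

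**2. When the rule can act before T1.** T1 is day 30 and the trigger needs 15 missing days. Only a lapse that starts by about day 30 − 15 = 15 can lead to exclusion before the primary outcome.

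- Intervention arm: forms are electronic and checked daily, so the lapse is visible as soon as 15 days are reached.
- Control arm: forms are on paper and first collected at the month-1 visit. The lapse first becomes visible there, and T1 can be completed at the same visit.

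For T2 and T3 both arms are exposed, because control lapses can be noticed at the visits from month 1 on.

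**3. Illustration of size.** Assumptions, none of them from the protocol: no true effect; SD 18.1; 20 per arm; k intervention patients and no controls excluded before T1; those excluded have the highest tendency to lapse; that tendency has correlation ρ with the supportive care needs score; two-sample t-test on the rest. Results are from simulation (40,000 to 100,000 replicates per scenario; a range is given where separate runs differ).

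| Excluded (k of 20) | ρ | Bias (points) | Type I error |
|---|---|---|---|
| 2, 4 or 6 | 0 | about 0 | about 5% |
| 2 | 0.3 | -1.0 | 5.4% |
| 2 | 0.5 | -1.6 | 6.0% |
| 4 | 0.3 | -1.8 | 5.8% to 6.0% |
| 4 | 0.5 | -3.0 | 8.0% to 8.3% |
| 4 | 0.7 | -4.2 | 11.4% to 11.6% |
| 6 | 0.3 | -2.5 to -2.6 | 6.8% to 7.1% |
| 6 | 0.5 | -4.3 | 10.6% to 10.9% |
| 6 | 0.7 | -6.0 to -6.1 | 16.9% to 17.0% |

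The bias can be checked by hand. With ρ = 1 and k = 4, the mean of the 16 patients kept falls by 0.334 SD. In this model the bias is proportional to ρ, so at ρ = 0.7 it is 0.7 × (−0.334) × 18.12 = −4.2 points, and at ρ = 0.3 it is 0.3 × (−0.334) × 18.12 = −1.8.

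A negative bias favours telenursing. The sign reverses if less needy patients are the ones who lapse, or if exclusions of needier patients fall mainly in control. Equal exclusion on the same basis in both arms would cancel it.

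Against the planned difference of 21.97 points, the bias with 4 excluded is 1.8/21.97 = 8% to 4.2/21.97 = 19%.

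**4. Power.** Under the plan's assumptions, power is 96.2% with 20 v 20 and 94.0% with 16 v 20. Loss of power is not the issue.

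**The case against.** The best defence is that exclusion from the study is not exclusion from the analysis. Section 2.7 names intention-to-treat and promises a missing-data method. Supportive care needs are measured at T0 in both arms, so an analysis as randomised with a method for missing outcomes stays possible. The article is also condensed, and analysis sets are commonly left to fuller documents. This stands so far as it goes: a reader might infer that the rule makes intention-to-treat impossible, and the text does not support that. But the exclusion rule is stated here, and a T1 score that was never sought can later be replaced only under assumptions that cannot be tested.

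A reader might also infer that the rule is bound to remove more intervention patients. The documents do not show this. The rule is permissive and names no arm. Intervention patients have daily review, a call at day 7 on procedures and e-tools, and telephone and message support, all of which could prevent lapses. Control patients work on paper without feedback and may lapse more. What is supported is the difference in when a lapse becomes visible.

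Nor can it be inferred that control lapses are never found. Nurses collect the forms monthly and enter them in a database, and the statement that the data are not evaluated may mean only that nobody acts on their content. Finally, the protocol does not say who decides on exclusion. It says only that healthcare professionals are unblinded.

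**Conclusion.** The point holds in a limited form. The protocol permits randomised patients to be excluded for missing data, does not extend intention-to-treat to them, and does not provide for their T1 to T3 assessment. The rule is discretionary and the setting open-label. Before T1 a lapse can trigger exclusion essentially only in the intervention arm, and only if it starts in about the first 15 days.

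Size and direction of bias cannot be derived from the document. The illustration runs from no bias (lapsing unrelated to needs), through about -1 point and 5.4% type I error (2 of 20 excluded, correlation 0.3), to -1.8 to -4.2 points and about 6% to 12% (4 of 20, correlation 0.3 to 0.7). The number excluded, the one-sided pattern and the correlation are all assumed. The problem is validity, not power or the drop-out allowance.

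**What to change.** Replace the exclusion sentence in section 2.5 with a statement that:

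- missing daily forms do not end study participation;
- T1, T2 and T3 questionnaires are sought from every randomised patient in both arms, by the mode planned for that arm (electronic link or paper), unless consent to data collection is withdrawn;
- all randomised patients are analysed in their assigned arm.

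Extend the intention-to-treat sentence in section 2.7 beyond abandonment to match, and report daily-form completion by arm.

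The cost is a one-paragraph amendment. No patients or visits are added, since both arms already attend monthly. Keeping each arm's planned mode avoids changing how the primary outcome is collected. The small downside is that some analysed patients will have incomplete daily data.
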